## Measurements

### Baseline assessment

Fall risk stratification will be performed in all potentially eligible patients using a Berg Balance Scale [18]. We will consider at medium-high risk of falls patients with a Berg Balance scale score ≤ 45 and/or at least one episode of fall within the last 12 months, as well as people presenting at least one fall episode undertaken during hospitalization in our Institute. Cognitive state will be evaluated using Mini Mental Test Examination (MMSE) [19].

In patients who have signed the informed consent, fear of falling, gait and balance problem, functional status and quality of life is assessed. Fear of falling will be measured by the Italian version of Falls Efficacy Scale (FES) [20], gait and balance by Timed Up and Go Test (TUG) [21] or Balance Evaluation System’s Test (BEST) in patients with Parkinson disease, functional state by Activities Daily Living scale (ADL), Barthel Index [22], Instrumental Activity Daily Living scale (IADL) [23] and quality of life by the EQ-5D questionnaire. Daily doses of drugs considered correlated with fall risk such as antihypertensive drugs, diuretics, beta-blocker, calcium antagonists, nitrates, antiarrhytmics, insulin, oral hypoglycemic drugs, neuroleptics, antidepressives, antiepileptic and dopaminergic and thyroid drugs will be also recorded.

The same operators previously involved in baseline evaluations will collect them at the end of 6-month follow-up as well.

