### Outcome measures

The primary outcome will be the proportion of fallers in the 6-month period after randomization. The secondary falls outcomes are the time between the first fall and the recurrent falls during follow-up and the percentage of patients sustaining two or more falls. A fall will be defined as “an event which results in a person coming to rest inadvertently on the ground or other lower level “ [24].

Other secondary outcomes include: changes in functional status (ADL, IADL and Barthel index), gait and balance measures (TUG or BEST test) and quality of life (EQ-5D).

The economic evaluations will be a combination of a cost-effectiveness and a cost-utility analysis [25] see list; we anticipated references [26]. The primary outcome measure for the cost-effectiveness analysis will be the percentage of people sustaining a fall during the 6-month follow-up. Within the cost-utility analysis the effects will be measured in terms of generic health-related quality of life descriptions, measured according to the standard Italian version of the EQ-5D [26], a self-administered questionnaire administered at baseline and after 6 months.

All healthcare and patient costs will be measured by means of a cost diary [27], in which participants continuously will record volumes of healthcare utilization during the 6 month follow-up period. In monthly telephone interviews, participants will be asked whether they had received care (or devices or services) or not. If participants will answer the question on a particular topic affirmatively, they will be asked to indicate the number of visits or details about the specific type of healthcare utilization. Data management will be organized “in-house”. Feasibility of the intervention program will be evaluated assessing participants compliance with the intervention protocol.

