### Data analysis

Data will be primarily analyzed according to the intention-to-treat principle.

An on-treatment analysis will be subsequently performed to assess whether protocol deviations have caused bias. Participants with documented deviation from the study protocol (i.e. patients in the intervention group who did not receive the entire intervention or participants in both groups with incomplete follow-up data) will be excluded from this analysis. Chi-square analysis will be used to compare the proportion of fallers and non-fallers between groups. Cox proportional hazards regression will be conducted with time to first fall within 6 months of follow-up as outcome measure with age, sex, anthropometric data, prevalent disease, comorbidities, residual disability, marital status, social and economic status, MMSE and baseline variables as covariates. Multiple linear regression analyses will be used to compare differences in the other secondary outcomes at 6 months follow-up between groups. ANOVA with repeated measures will be used to analyze differences between groups from baseline to follow-up. Differences in baseline characteristics between groups will be examined using parametric (*T*-test) and non-parametric (Chi-square) tests. No ad interim analysis will be performed.

The economic evaluations will be conducted from a societal perspective and involve calculating cost-effectiveness ratio. The incremental costs and effects of the intervention will be compared with control group. The alfa level for all analyses is set at 0.05. Statistical analyses will be performed using STATA 13 program.

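### Two-time-point secondary outcomes appear to get both a 6-month regression and a repeated-measures ANOVA with no stated lead; one baseline-adjusted regression should be named as the main analysis

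*Protocol article*

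**What the plan says.** The Outcome measures section of the protocol article lists, as further secondary outcomes, "changes in functional status (ADL, IADL and Barthel index), gait and balance measures (TUG or BEST test) and quality of life (EQ-5D"). Each is measured twice. For the functional and balance measures, the Baseline assessment section says: "The same operators previously involved in baseline evaluations will collect them at the end of 6-month follow-up as well". The EQ-5D is described as "a self-administered questionnaire administered at baseline and after 6 months".

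The Data analysis section then gives two methods in consecutive sentences. The first is "Multiple linear regression analyses will be used to compare differences in the other secondary outcomes at 6 months follow-up between groups". The second is "ANOVA with repeated measures will be used to analyze differences between groups from baseline to follow-up". The regression sentence names no covariates; the covariate list in that section, which ends "social and economic status, MMSE and baseline variables as covariates", belongs to the Cox model for time to first fall. The ANOVA sentence names no outcome. On significance, the section says: "The alfa level for all analyses is set at 0.05". Nothing ranks the two methods.

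**The concern.** The two methods target different contrasts. The regression compares groups on the 6-month value; the ANOVA, read as a comparison from baseline to follow-up, compares them on change. They can disagree, and the text does not say which result would then be the trial's answer for that outcome.

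Two things are at stake. The first is precision: neither method, as worded, commits to the analysis that makes best use of a baseline value already collected. The second is selection: two tests at 0.05 on each of several outcomes leave room to report the more favourable one. Because EQ-5D also supplies the effect measure in the cost-utility analysis, a chance baseline imbalance that is not adjusted for properly would carry into that result too.

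**Working it through.** **Inputs from the protocol article.** Two measurements per outcome (Baseline assessment; Outcome measures). 145 patients per group and about 6% dropout (Sample size), so 145 × 0.94 = 136.3, about 136 analysed per group. Alpha 0.05 (Data analysis); sidedness is not stated, and two-sided is assumed here.

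**Assumptions.** The document gives neither the correlation rho between baseline and 6-month values nor any SD for these outcomes. A range of rho is therefore shown, with the same SD (sigma) at both times. An effect of 0.3 SD is used only to express precision as power. There is no plan figure to reproduce first, because the only sample-size calculation is for fallers.

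**Step 1: what the ANOVA tests.** With two time points, the group-by-time test of a repeated-measures ANOVA is identical to a t-test on the change from baseline.

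**Step 2: variance of the treatment effect.** With n per group the variance is (2/n) × v, where

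- 6-month value only: v = sigma²
- change score (ANOVA group-by-time): v = 2·sigma²·(1 − rho)
- regression adjusted for baseline: v = sigma²·(1 − rho²)

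Change score relative to adjusted: 2(1 − rho)/(1 − rho²) = 2/(1 + rho), which exceeds 1 for every rho below 1. 6-month value only relative to adjusted: 1/(1 − rho²), which exceeds 1 for every rho above 0 (and below 1).

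**Step 3: numbers** (power at 136 per group, 0.3 SD, two-sided 0.05).

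| rho | ANOVA / adjusted variance | 6-month only / adjusted variance | Power: ANOVA | Power: 6-month only | Power: adjusted |
|---|---|---|---|---|---|
| 0.3 | 1.54 | 1.10 | 55% | 70% | 74% |
| 0.5 | 1.33 | 1.33 | 70% | 70% | 82% |
| 0.7 | 1.18 | 1.96 | 89% | 70% | 93% |
| 0.9 | 1.05 | 5.26 | about 100% | 70% | about 100% |

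The adjusted model is the most precise of the three throughout. Between the other two, the ANOVA has the smaller variance when 2(1 − rho) < 1, that is, when rho is above 0.5; below 0.5 the 6-month-only comparison does.

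**Step 4: two tests, either one reportable.** In a simulation with no treatment effect (10,000 runs for each of the four rho values, normal data, 136 per group), the chance that at least one test is significant at 0.05 was 5.8% to 7.6% for ANOVA plus adjusted regression, and 8.7% to 9.4% for ANOVA plus unadjusted 6-month regression. These are per-outcome rates.

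**The case against.** The strongest reply is that much of this belongs in a statistical analysis plan. A journal article need not list the covariates of a secondary regression, and a multiple regression may well include the baseline value. If it does, the efficient analysis is already planned and no precision is lost in it. That stands as far as it goes: the unnamed covariates alone would not be a finding. What remains is that the article itself commits to two methods for what looks like one question, without an order between them.

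The overlap of outcomes is also an inference, since the ANOVA sentence names none. It is a sound one: these are the listed secondary outcomes with both a baseline and a 6-month value.

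Three stronger readings are tempting, and the document does not support them.

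- A reader might infer that the ANOVA is the weaker of the two planned analyses. That is assured only if the regression includes the baseline value, which is not stated. If it does not, the ANOVA is the more precise one when rho is above 0.5 (89% against 70% power at rho 0.7).
- A reader might object that the ANOVA's group main effect averages in the baseline and so estimates half the 6-month difference. That is true of the main effect, but the wording about differences from baseline to follow-up points to the group-by-time term, and the plan does not name the main effect as its test.
- A reader might turn the variance ratios into patients lost to the trial. They compare methods at assumed correlations, shrink to about 5% at rho 0.9, and concern outcomes on which the trial was not sized.

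The selection risk is moderate, and it applies to secondary outcomes only.

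**Conclusion.** The point holds in a limited form. Two analyses, both at 0.05 and with no stated lead, most naturally apply to the same two-time-point secondary outcomes, and neither is stated to be the baseline-adjusted regression that would serve best. Relative to that model, the change-score test carries 5% to 54% more variance for rho from 0.9 down to 0.3; an unadjusted 6-month regression, if that is what is meant, is less precise at any positive rho. Leaving the choice open raises the per-outcome type I error from 5% to roughly 6–9%. These sizes rest on assumed correlations, equal SDs at the two times and, for the error rates, normal data. The ranking of the adjusted model as most precise holds for any rho between 0 and 1 under equal SDs. The primary comparison of fallers by chi-square is untouched.

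**What to change.** In the Data analysis section, replace the two sentences with one main analysis for each continuous secondary outcome: a linear regression of the 6-month value on randomised group and the baseline value of the same measure, reported as the adjusted mean difference with its 95% confidence interval. Either delete the repeated-measures ANOVA or state that it is supportive only and that conclusions rest on the regression. If further covariates are wanted, name them in advance; the open-ended Cox list should not be carried over, because it would reopen the choice that the change is meant to close. State that the EQ-5D effect in the cost-utility analysis is adjusted for baseline EQ-5D in the same way.

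The cost is a few lines of text. The baseline values are already collected, and no visit, patient or measurement is added. The Progress of the study section places the start of data analysis after follow-up ends, so on the article's own timeline the choice can be fixed before results are seen.

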### Progress of the study

Recruitment of eligible subjects started in April 2014 and ended in December 2015, resulting in a total of 290 patients enrolled in the trial. The follow-up will end in June 2016 and then data-analysis will be initiated.

## Discussion

The main strengths of this study are the target population and the administration of the prevention program.

Despite evidence of the effectiveness of falls prevention activities for community-dwelling older people, the applicability of these interventions has not, to date, been specifically evaluated in elderly population affected by multiple comorbidity, discharged from a multispecialistic rehabilitation medical setting. The inclusion of patients with mild-moderate cognitive impairment represents a further originality. In fact, most studies conducted in community-dwelling patients have not specifically addressed older adults with cognitive impairment, and the effectiveness of fall prevention interventions in this population is not known [9]. Elderly adults with cognitive problems are one of the most vulnerable sectors of our society with clear mental, social, and physical disadvantages. They are more likely to experience falls, and experience further mobility decline due to having fallen; therefore it is urgent to identify evidence based interventions for reducing the risk of falls and related injuries in people with cognitive impairment.

Finally, an additional strength of the study is the administration of a fall prevention program supported by the new home-based technologies. This may contribute to a new approach to prevent and treat fall risk in this population. To date, no adequately powered studies have investigated the effect of the Information and Communication Technologies (ICT) in a home fall prevention program. We aim the program will be feasible in terms of intensity and characteristics, but particularly in terms of patient and provider compliance, which represent a possible barrier in successful implementation of fall prevention strategies [9].

Furthermore, the results of the economic evaluation could provide information about the cost-effectiveness of the intervention and the effects on quality of life. In case of shown effectiveness and cost effectiveness, the program could be implemented into health services settings.

All results from the study will be communicated by publication without any restriction.

### Limitation

The main potential critical aspect of our study is the sample size calculation. Epidemiological data on prevalence and fall rate incidence of subjects with a high fall risk profile coming from a multispecialistic rehabilitation setting are lacking. Consequently, we powered the study on the fall rate observed in a small number of patients discharged from our Institute that we hope will be confirmed in the usual care group.

## Abbreviations

BEST: Balance evaluation system’s test
FES: Falls efficacy scale
GPs: General practitioners
IADL: Instrumental activity daily living scale
ICT: Information and communication technologies
MMSE: Mini-mental state examination
NT: Nurse tutor
RCT: Randomized controlled trial
TUG: Timed up and go test
WHO: World Health Organization
